### Safety and adverse event monitoring

There will be a low probability of adverse events in this study. Potential risks are skin irritation, redness, scratching, dizziness, and seizures. Any adverse events during the study should be recorded, observed, and followed up in detail, including whether the adverse event is quantitatively related to mirror therapy, whether symptoms resolve or disappear after stopping treatment, and whether appropriate treatment has been administered. The questionnaires will be administered to the participants after every treatment, and the results will be recorded and analyzed. The outcome assessors will judge the severity (mild, moderate, or severe), seriousness, and causality (definitely related, probably related, possibly related, possibly not related, definitely not related to the intervention, or not assessable). In severe cases, more moderate interventions are required to prevent overwhelming the patient’s body. In the event of severe adverse reactions or worsening of the condition, immediate termination of the experiment and prompt reporting to the ethics committee are essential. In addition, a Data Monitoring Committee (DMC) will help finalize interim analyses or stop rules. The DMC is composed of clinicians and statisticians, independent of the sponsor and study team. It scrutinizes accumulated data and recommends modifications for future trials, ensuring risks to participants remain within limits. The DMC can discontinue a trial if significant protocol infractions transpire or large patient dropouts occur. Should any participants suffer any harm from the trial, they will receive necessary medical treatment for the injury or complication, free of charge, as a public patient within the Second Affiliated Hospital of Chongqing Medical University. This safeguard aims to protect the health and safety of participants and provide necessary medical care.

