## Methods/design

### Study design

This is a single-center, prospective, single-blinding, randomized controlled superiority trial. The objective will be used to evaluate the effectiveness of TBMT (using a newly designed mirror) compared to conventional occupational therapy on upper extremity functions of stroke patients. Patients will be randomly allocated in a 1:1 ratio into a control (*N* = 25) or TBMT group (*N* = 25), with the control group receiving conventional occupational therapy intervention and TBMT group receiving task-based mirror therapy in addition to CG. A professional team will measure relevant outcomes at baseline and 4 weeks after treatment.

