### Randomization and blinding

A total of 50 patients who meet the inclusion criteria will be randomly assigned to either the task-based mirror group or the control group. The randomization sequence will be generated by an independent statistician using SPSS Version 19.0. Patients will be assigned randomization numbers based on the order of enrollment. To maintain blinding, opaque sealed envelopes will be utilized to conceal group assignments. Patients will only become aware of their group after opening the envelope, which will be securely stored in a separate cabinet. Blinding of evaluators will be employed in this study to avoid bias stemming from subjective factors. The same investigator, who will be blinded to the treatment assignment, performed all the assessments. Additionally, statisticians will conceal the groupings and their significance, and the code will remain undisclosed until the analysis is finalized. In case of a severe incident during a trial, blinding may need to be undone for proper treatment. This decision must be endorsed by the trial’s lead researcher/medic, and recorded in the protocol, with utmost consideration given to minimizing bias and ensuring data quality.

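### Giving the causality judgement of adverse events to the outcome assessors may reveal the arm to the blinded FMA-UE rater for patients who have an event

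*Protocol article*

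**What the plan says.** Study design describes the trial thus: "This is a single-center, prospective, single-blinding, randomized controlled superiority trial". Randomization and blinding says where the blind lies and why: "Blinding of evaluators will be employed in this study to avoid bias stemming from subjective factors". It adds: "The same investigator, who will be blinded to the treatment assignment, performed all the assessments". Patients are not blinded to treatment: "Patients will only become aware of their group after opening the envelope". The section foresees one way of lifting the blind: "In case of a severe incident during a trial, blinding may need to be undone for proper treatment". That step needs the endorsement of the lead researcher or physician and must be documented.

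Safety and adverse event monitoring allots a further task by role: "The outcome assessors will judge the severity (mild, moderate, or severe), seriousness, and causality". Causality is graded on a scale that runs from definitely related to "definitely not related to the intervention, or not assessable". Earlier in the same section, the details to be recorded for each event include "whether the adverse event is quantitatively related to mirror therapy" and whether symptoms clear once treatment is stopped. Questionnaires are taken from participants after each session. The section expects adverse events to be unlikely and gives no rate.

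**The concern.** The two sections assign tasks to what reads as the same role, and the tasks do not fit together. The arms are visibly different: one uses the mirror device and the other has occupational therapy without it. A rater who must grade whether an event was caused by study treatment, alongside a record that asks about mirror therapy, may learn which treatment the patient had.

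FMA-UE is scored item by item as 0, 1 or 2, with a judgement between partial and near-normal performance. ARAT and MBI are also scored by a rater. Events in the four treatment weeks come before the 4-week and later ratings, so any knowledge gained would be present when those scores are given. With one rater for all patients, no second rater would dilute a leaning. The blinding section lets the blind be lifted only for a severe incident and with endorsement. The causality task could lift it for any event, including a mild one, with no endorsement and no record.

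**Working it through.** **The passages side by side**

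1. Who scores outcomes: one investigator, blinded to assignment (Randomization and blinding).
2. Who judges adverse events: the outcome assessors (Safety and adverse event monitoring). No separate safety assessor is named, and no step masks the arm in the adverse event material.
3. What the event record holds: relation to mirror therapy, and resolution after treatment is stopped (same section).
4. Who receives mirror therapy: the TBMT arm only (Control group; Task-based mirror therapy).

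From 1 to 4 there are two possibilities. If the assessor stays blind, a grade of relatedness to mirror therapy carries little information, because the assessor does not know whether the patient had any. If the assessor learns the arm, the statement in 1 no longer holds for that patient.

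**Scale of the outcome, from the plan's own figures**

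- Target difference 9 FMA-UE points, d = 1.13 (Sample size estimation). Implied SD = 9 / 1.13 = 7.96.
- The stated total of 44 reproduces: a two-sided two-sample t test at alpha 0.05 and power 0.95 needs 21.36, so 22 per arm. The present point does not alter it.
- With 25 per arm, the standard error of the difference is 7.96 × √(2/25) = 2.25 points.

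**Possible bias in the TBMT mean**

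Bias = (share of TBMT patients unmasked) × (over-scoring per unmasked patient).

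- Over-scoring per unmasked patient, assumed: 1 item in 10 raised by one point. FMA-UE has 33 items, so 33 / 10 = 3.3 points.
- Share unmasked, assumed because no event rate is given: 10% to 20%.

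| Share unmasked | Bias in TBMT mean | As a share of 9 points | In standard errors |
|---|---|---|---|
| 10% | 0.10 × 3.3 = 0.33 | 0.33 / 9 = 3.7% | 0.33 / 2.25 = 0.15 |
| 20% | 0.20 × 3.3 = 0.66 | 0.66 / 9 = 7.3% | 0.66 / 2.25 = 0.29 |

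For reference, a mean bias of 1 full point with 25 per arm would raise the two-sided type I error from 5% to about 7%. The values in the table lie below that. They count the TBMT arm only; unmasked control patients are left out.

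**The case against.** **Disclosure is inferred.** The sentence that names the outcome assessors asks about relation to the intervention. The article also calls the control treatment an intervention, and the scale allows a grade of not assessable. A blinded rater could grade relatedness to study treatment in general. The mirror therapy wording comes from a separate sentence that does not say who writes or reads the record, and nothing says the assessor receives the allocation list. This stands, so the point is that the task may reveal the arm. It does not remove the conflict, because no other reader of the record is named and nothing keeps the record from the assessor.

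**The rater's identity is not fully settled.** Study design speaks of a professional team, Outcome measurements of evaluators, and the safety section of assessors in the plural. If several people share the role, the person who grades an event need not be the FMA-UE rater. The blinding section, however, says that one investigator does all assessments, and no text separates the two tasks. This is a further reason to state the roles.

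**Stronger readings.** A reader might infer three things that the documents do not support:

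- That the rater is exposed to 20 questionnaires per patient. Five days a week for four weeks does give 20 sessions, but the article does not say who administers the questionnaires, who sees them or whether they name the arm.
- That the result could be biased by 3.3 points, or 37% of the 9-point target. That would need every TBMT patient to be unmasked and over-scored, whereas this route reaches only patients with an event.
- That assessor blinding is the trial's only protection against bias. The plan also has a sequence generated by an independent statistician, opaque sealed envelopes, and statisticians who do not know the group codes. None of these protects the scoring itself.

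**Blinded causality judgement has value.** Staff who know the arm, in a team that designed the device, may judge its harms less neutrally. This stands as a small cost of the fix.

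**Conclusion.** The point holds as a conflict of roles in the current text. Followed as written, the safety section opens an uncontrolled route by which the FMA-UE rater may learn the arm of patients who have an adverse event.

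The likely effect on the primary comparison is small: about 0.3 to 0.7 FMA-UE points in the TBMT mean. This rests on two assumptions that the documents do not supply, namely that 10-20% of TBMT patients are unmasked and that each is over-scored by 3.3 points. With fewer events it would be smaller. The change is still worth making, because for rater bias assessor blinding is the only safeguard described and the correction is simple.

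**What to change.** Reconcile the Randomization and blinding section with Safety and adverse event monitoring:

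- Assign the judgement of severity, seriousness and causality to existing study staff who do not score outcomes, and name that role in the safety section.
- State that adverse event forms and session questionnaires are kept from the FMA-UE rater.
- As an optional extra, have the rater record a guess of allocation at the week-4 assessment, so that the blind can be examined afterwards.

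The cost is a task moved between existing staff and, for the optional extra, one line on a form. No patients, visits or analyses are added. The drawback is that causality may be judged by people who know the arm. Where staffing allows, someone not involved in developing the device would lessen it.

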### Statistical analysis

Data management and analysis will be conducted in SPSS version 23. Groups will be compared at baseline using the *t* test for independent samples for the continuous variables, and the chi-square test for categorical data. The differences of the outcomes, including the FMA-UE, MBI, ARAT, and the 9HPT, between the groups at each of the trial time points will be analyzed using mixed-design 2-way repeated-measures analysis of variance (ANOVA), taking time (4 levels: preintervention, after 2 weeks, after 4 weeks of intervention and 3 months at the end of the trial for follow-up) as the within-subject factor and group (2 levels: TBMT and CG) as the between-subject factor. If participants drop out during the intervention period, they will not be excluded due to the principle of intention to treat (ITT). Furthermore, in instances of missing data, the continuation of observations (LOCF) method will be employed, whereby the last recorded observation preceding the gap in data will serve as a substitute. Unfavorable stroke outcomes correspond to lower FA values for corticospinal tracts, while robust functional recovery denotes elevated FA values. Subgroup analyses of FA values will be conducted based on the interquartile spacing (< 25% interval; 25–75% interval; > 75% interval) method post the inclusion of all individuals to standardize the baseline conditions of the patients. We will use linear regression model outcomes at 4 weeks post-treatment cessation as the dependent variable (FMA-UE). This model will include treatment assignment (TBMT vs. CT) and baseline outcome measure as fixed-effects, as well as patient characteristics (low or high impairment severity at baseline). We will examine differential impacts by fitting separate models with treatment-impairment severity. We will report relevant point estimates and standard errors for these models and conduct 5% level tests for interaction terms with two-sided alternative hypotheses. A *p*-value < 0.05 is deemed a statistically significant discrepancy.

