**Methods and analysis:**

This single-center randomized controlled trial will involve 50 patients with stroke. All patients will be randomly assigned to either the task-based mirror therapy or the control group. The interventions will be performed 5 days per week for 4 weeks. The primary outcomes will be the mean change in scores on both the FMA-UE and modified Barthel Index (MBI) from baseline to 4 weeks intervention and at 12 weeks follow-up between the two groups and within groups. The other outcomes will include the Action Research Arm Test (ARAT), the Nine Hole Peg Test (9HPT), the Functional Independence Measure, and MRI.

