### Sample size estimation

The sample size was derived from pre-existing research using G Power v.3.1, considering significance level (*α*) = 0.05, power (1 − β) = 0.95, and given that the minimal clinically significant difference in patient’s hand function improvement, as per prior study data, is 9 points in the FMA-UE with an effect size of *d* = 1.13 [14]. Estimation via G Power software yielded a requirement of 44 samples. Considering potential subject attrition or termination, the sample size could be augmented by 10–15%, resulting in the adjusted sample size of *N* = 50, or 25 patients in each group. Consequently, the total sample size for both groups was formulated as 50.

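### The FMA-UE repeated-measures ANOVA takes the pre-treatment score as a time level and names no term or contrast as the primary test; the second FMA-UE model is unranked and dated to no analysis visit

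*Protocol article*

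**What the plan says.** Four parts of the protocol article bear on the FMA-UE test.

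- **Statistical analysis, main model.** Differences in FMA-UE, MBI, ARAT and 9HPT "between the groups at each of the trial time points will be analyzed using mixed-design 2-way repeated-measures analysis of variance (ANOVA"), with group as the between-subject factor. The four levels of time are "preintervention, after 2 weeks, after 4 weeks of intervention and 3 months at the end of the trial for follow-up". No term or contrast is singled out as the primary test.
- **Statistical analysis, second model.** A linear regression of FMA-UE is planned at a time described as four weeks after treatment has stopped. "This model will include treatment assignment (TBMT vs. CT) and baseline outcome measure as fixed-effects", along with baseline severity. It serves to examine differential effects by severity and is not called primary. The "5% level tests for interaction terms with two-sided alternative hypotheses" belong to these treatment-by-severity models, not to the group-by-time term.
- **Abstract.** "The primary outcomes will be the mean change in scores" on both FMA-UE and MBI, to week 4 and at 12 weeks. The Primary outcomes section names FMA-UE alone, without a time, and MBI is listed under Secondary outcomes.
- **Sample size estimation.** The inputs are "significance level (*α*) = 0.05", "power (1 − β) = 0.95" and a target that "is 9 points in the FMA-UE", with d = 1.13. The result is 44, raised to 50 for attrition.

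**The concern.** The trial is sized on one two-group difference, and the primary outcome is stated as a change. The main model is a four-level ANOVA that can yield several different FMA-UE tests:

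- The group main effect averages over all four times, including a baseline at which randomised arms should not differ.
- A comparison of raw scores at each time is not a comparison of change.
- The group-by-time term does address differential change. It is a 3-df omnibus test, so it says neither when the arms differ nor by how much.

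The regression adds a further FMA-UE result. With no ranking, the choice among these results could be made after the data are seen. One of the candidates, the group main effect, could also miss the planned effect.

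**Working it through.** **1. Reproduce the plan's figure.** The implied SD is 9/1.13 = 7.96 points. A two-sample t test at two-sided 5% with d = 1.13 has 94.7% power with 21 per arm and 95.6% with 22, so 44 in total, as stated. A one-sided test would need 18 per arm (36), so the calculation was two-sided. Going from 50 to 44 is 12% attrition, inside the stated 10–15%.

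**2. Assumptions needed beyond the document.** The protocol gives neither the correlation between visits nor the course of the effect. It also does not say whether 7.96 is the SD of the final score or of the change. I take compound symmetry with correlation ρ from 0.3 to 0.9, no difference at baseline, and an effect of 0, half, full, full at the four times. With σ the SD at a single visit, σ = 7.96 under the final-score reading and σ = 7.96/√(2(1 − ρ)) under the change reading.

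**3. Group main effect.** It estimates (0 + 0.5 + 1 + 1)/4 = 0.625 of the week-4 difference, or 0.625 × 9 = 5.6 points. The SD of a patient's four-visit mean is σ√((1 + 3ρ)/4). Standardised effects:
- ρ = 0.5, either reading: 5.625/(7.96 × 0.791) = 0.89
- ρ = 0.7, final-score SD: 5.625/(7.96 × 0.880) = 0.80
- ρ = 0.7, change SD: 5.625/(10.28 × 0.880) = 0.62
- ρ = 0.3, change SD: 5.625/(6.73 × 0.689) = 1.21

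**4. Group-by-time term.** Noncentrality is (n/2)Σc²/(σ²(1 − ρ)), where c is the deviation of each visit's effect from the mean effect. Here Σc² = 5.625² + 1.125² + 2 × 3.375² = 55.7. Under the change reading σ²(1 − ρ) = 7.96²/2 = 31.7 for every ρ, so noncentrality is 11 × 55.7/31.7 = 19.3 on 3 and 126 df.

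**5. Baseline-adjusted week-4 difference.** Residual SD is σ√(1 − ρ²), with 41 df. The lowest power is at ρ = 0.9 under the change reading, where 9/(17.81 × 0.436) = 1.16.

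Power (%) at 22 per arm:

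| ρ | Main effect, final-score SD | Main effect, change SD | Group × time, final-score SD | Group × time, change SD | Adjusted week 4, final-score SD | Adjusted week 4, change SD |
|---|---|---|---|---|---|---|
| 0.3 | 91.3 | 97.5 | 88.1 | 96.6 | 97.0 | 99.5 |
| 0.5 | 82.5 | 82.5 | 96.6 | 96.6 | 98.8 | 98.8 |
| 0.7 | 73.9 | 52.1 | 99.9 | 96.6 | 99.9 | 97.8 |
| 0.9 | 66.3 | 18.6 | 100.0 | 96.6 | 100.0 | 96.4 |

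A simulation of 20,000 trials at ρ = 0.5 and 0.7 (final-score reading) gave 82.6% and 74.0% for the main effect, and 98.8% and 99.9% for the adjusted difference.

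**6. Sensitivity to the effect profile.** With the full effect from week 2, the main effect estimates 0.75 of the difference (6.75 points), and its power at ρ = 0.5 rises to 93.5%. If half the effect is lost by follow-up, the group-by-time power falls to 88.7% (change SD).

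**7. Time point of the regression.** Treatment lasts four weeks, so four weeks after it stops is about week 8. That is none of the four ANOVA times, and it is not among the visits under Outcome measurements. The closing sentence of Study design is worded so that it could mean either the end of the four-week course or four weeks beyond it, so it does not settle the matter.

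**The case against.** A reader might infer that the planned analysis is underpowered and cannot estimate the primary outcome. The document does not support this, for four reasons, all of which stand.

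- The low power belongs to the group main effect, which the protocol never makes decisive. In a pre/post design the usual treatment test is group-by-time, which holds 96.6% under the change reading.
- The same ANOVA layout contains a contrast of week 4 minus baseline between arms, which is the difference in mean change. If 7.96 is the SD of change, it has 95.6% power at 22 per arm, exactly the sizing calculation. The contrast is unspecified, not unavailable.
- The shortfall rests on an assumed correlation and effect profile, and at ρ = 0.3 it can vanish (97.5%, change SD). If dropouts are retained as planned, up to 25 per arm would be analysed. This helps a little: at ρ = 0.7 under the change reading the main effect goes from 52.1% to 57.7%.
- Baseline adjustment is not absent, because the regression already includes it.

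Nor can one say that the stated primary outcome is change at week 4 alone, since the abstract names two times and two measures. Handling of sphericity is commonly left to a SAP and is not part of this point.

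None of this says which FMA-UE result decides. That is not detail deferred to a SAP, because the article itself states the model, its time levels, the regression and the sizing comparison, and leaves them unconnected.

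**Conclusion.** The point holds as a failure to fix the primary test, not as a demonstrated loss of power. The main FMA-UE model has no designated term or contrast, and a second FMA-UE model stands beside it, unranked and at a time that is not an analysis visit. Under the assumptions in the working, the group main effect, if chosen, would recover 0.625 of the week-4 difference. It would have less than 95% power at 22 per arm for every correlation of 0.5 or more that was checked. The group-by-time test is adequately powered in most of these cases but supplies no estimate at week 4 or 12 weeks. The baseline-adjusted week-4 difference has at least 96% power under either SD reading across correlations of 0.3 to 0.9. It needs at most 21 per arm for 95%, so the planned number is sufficient.

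**What to change.** - Name one primary analysis: the baseline-adjusted group difference in FMA-UE at week 4 (end of treatment), two-sided 5%, with 95% CI. Take it from a model of the post-baseline visits with baseline FMA-UE as a covariate, not as an outcome level, and with group, visit and group-by-visit terms. Take the 12-week difference from the same model.
- Reconcile the abstract with the outcome sections on whether MBI and the 12-week time point are primary. Making FMA-UE at week 4 the single primary test narrows what the abstract now says, and the text should state this openly.
- Correct the regression's time point to a listed visit and label that model secondary or sensitivity.
- Reconcile the week-2 assessment, which appears only under Statistical analysis, with the visits under Outcome measurements. State whether last-observation carry-forward still applies, since the suggested model can use incomplete follow-up without it.
- Keep the ANOVA as supportive only.

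The cost is protocol wording. The baseline score is already collected, the named software can fit the model, and N = 50 does not change.

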### Participants

Fifty eligible patients with upper limb motor dysfunction in stroke will be recruited from the outpatient and inpatient departments of the Department of Rehabilitation Medicine, Department of Neurology, and Department of Neurosurgery of the Second Hospital of Chongqing Medical University. Eligible patients had to satisfy the inclusion, exclusion criteria, and termination criteria (Table 1). Information about this trial will be posted via posters in the waiting area of the Rehabilitation Department and the Rehabilitation Medicine Clinic so that interested patients can contact the program director through their therapist. If an applicant meets the study criteria, then they will be invited to participate

**Table 1 Tab1:** Inclusion, exclusion criteria and termination criteria

**Inclusion criteria** 1. Meet the diagnostic criteria for stroke (including cerebral hemorrhage and cerebral infarction) formulated by the 4th National Cerebrovascular Disease Conference in 1995and confirmed by head CT or MRI, and the course of the stroke is 1 to 6 months 2. Abnormal hand function after stroke, Brunnstrom stage I-III, upper limb FMA-UE score lower than 47 3. The contralateral hand is in good condition 4. The age of the patient is 20-80 years old, and the gender is not limited 5. No progressive stroke performance, stable vital signs 6. Cognitive function is relatively intact, MMSE>17 or MoCA>24 7. Be able to follow the clinical treatment plan and sign the subject's informed consent
**Exclusion criteria** 1. Subjects with upper limb dysfunction before stroke 2. Subjects with visual impairment or unilateral neglect 3. Severe cognitive impairment or poststroke depression 4. Metal implants in the body, such as cardiac pacemakers and other metal devices 5. Suffering from serious underlying diseases, such as heart function level 4 (NYHA) or severe COPD 6. Subjects participating in other clinical trials at the same time 7. Subjects judged to be unsuitable for this trial, and withdrawing voluntarily 8. Subjects unable to undergo MRI scans
**Termination criteria** 1. Subjects have serious adverse events or adverse reactions 2. Subjects have other changes in their condition and cannot continue the trial 3. Subjects have significant problems in the design of the protocol or the trial and are unable to determine the efficacy

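### The repeated-measures ANOVA over four unequally spaced visits names no sphericity correction or covariance model; if uncorrected p-values are read and individual change spreads over time, its 5% group-by-time test runs at about 6-10%

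*Protocol article*

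**What the plan says.** The Statistical analysis section sets one test for FMA-UE, MBI, ARAT and 9HPT: a "mixed-design 2-way repeated-measures analysis of variance (ANOVA), taking time (4 levels: preintervention, after 2 weeks, after 4 weeks of intervention and 3 months" as the within-subject factor, with "group (2 levels: TBMT and CG) as the between-subject factor". The software is given ("Data management and analysis will be conducted in SPSS version 23") and so is the criterion ("A *p*-value < 0.05 is deemed a statistically significant discrepancy"). The section does not mention sphericity, a degrees-of-freedom correction, the multivariate test or a covariance structure. It does not say that the uncorrected row will be read, and it names no error term for comparisons at a visit.

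Three other statements bear on the point:

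- The same section adds a linear regression of FMA-UE at one post-treatment time point, with treatment and baseline value as terms.
- Table 1 under Participants admits patients when "the course of the stroke is 1 to 6 months".
- The visit schedule differs between sections. Statistical analysis has four time points, Outcome measurements has three (baseline, 4 weeks, 12 weeks) and Study design has two (baseline, 4 weeks).

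**The concern.** With more than two time levels, the univariate F tests for time and group-by-time have their nominal size only under sphericity, meaning that the difference between any two visits has the same variance. Here that would require individual change to vary as much over 2 weeks as over about 3 months, in patients who are still recovering at different rates. That is hard to believe.

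When sphericity fails, the uncorrected F test is liberal. MBI, ARAT, 9HPT and the follow-up comparison of FMA-UE all rest on this ANOVA, and the Abstract lists change in FMA-UE and MBI to 4 and 12 weeks as primary. SPSS prints uncorrected, corrected and multivariate results together, so a plan that does not name the operative row leaves that choice open until the results are visible.

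**Working it through.** **The plan's own figure.** Sample size estimation is made "considering significance level (*α*) = 0.05, power (1 − β) = 0.95", for "9 points in the FMA-UE with an effect size of" d = 1.13. A two-sided two-sample t test gives 22 per arm, or 44 in total (power 0.956), which matches the stated 44. The implied SD is 9/1.13 = 7.96 points. The calculation uses no between-visit variance or correlation, so everything below needs an assumed covariance.

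**Formulas.** Let Σ be the covariance matrix of the k visits, C the centring matrix and M = CΣC with non-zero eigenvalues λ. The Greenhouse-Geisser value is ε = tr(M)² / [(k−1) tr(M²)]. With 25 per arm there are 48 between-subject degrees of freedom. The true size of the uncorrected test is P[Σλχ²₁ / (Σλχ²₄₈/48) > F(0.95; 3, 144) = 2.667]. If the pooled error were used for one contrast, the ratio of its SE to the true SE is √(mean variance of all pairwise visit differences / variance of that difference).

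**One case in full.** Assume a random walk in recovery, SD of 4-week change 7.96, measurement-error SD 2 and visits at weeks 0, 2, 4 and 12.

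- Walk variance per week: (7.96² − 2×2²)/4 = (63.36 − 8)/4 = 13.84.
- Variance of a difference at lag L: 13.84L + 8. This gives 35.7 (lag 2, occurring twice), 63.4 (lag 4), 118.7 (lag 8), 146.4 (lag 10) and 174.1 (lag 12).
- The 3-month difference has 174.1/35.7 = 4.9 times the variance of a 2-week difference. Sphericity requires a ratio of 1.
- ε = 0.60; size of the uncorrected 5% test = 7.6%.
- Mean of the six variances = 95.7; pooled/true SE at the last visit = √(95.7/174.1) = 0.74.

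**Range over assumed covariances** (four visits, last at week 12 or 16, no treatment effect, uncorrected test):

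| Assumed covariance | Size | Pooled/true SE, last visit |
|---|---|---|
| Compound symmetry, equal SDs | 5.0% | 1.00 |
| Compound symmetry, rising SDs | 5.0-5.9% | 0.81-0.98 |
| Strong patient effect + AR + noise | 5.4-5.5% | not computed |
| Random slopes, weak to strong | 5.2-7.6% | 0.73-0.91 |
| AR(1) by visit, or in weeks with weekly ρ 0.8-0.99 | 6.0-8.5% | 0.72-0.86 |
| Random walk or saturating recovery, SD 7.96, error SD 2-3 | 7.0-10.4% | 0.62-0.76 |
| The same, error SD 4 | 6.2-7.9% | not computed |
| Mathematical ceiling (ε = 1/3) | 10.9% | not computed |

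**Other schedules.** With three visits the size is 5.0-6.6% over the first set of structures and 5.4-8.1% over structures with growing spread. With two visits it is 5.0%, because there is only one difference.

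**After correction.** Greenhouse-Geisser, Huynh-Feldt or the multivariate test gives 4.4-5.5% in every case where it was tried.

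**The case against.** The strongest objection is that the point rests on silence. The article never says the uncorrected F test will be used, SPSS offers the corrections, and the choice of row is a detail that an article may leave to an analysis plan not shown here. This stands to the extent that the inflation cannot be stated as fact. It does not dispose of the point, because the method that is named suits these visits poorly and a better one is available in the same software.

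Several stronger readings are tempting but unsupported:

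- **Unequal spacing alone breaks sphericity.** It does not: compound symmetry gives 5.0% at any spacing. The violation comes from spread in individual change growing with time, which is plausible but not documented.
- **The test runs at 7-10%.** That needs a recovery model in which growth dominates noise. The article does not say that 7.96 is the SD of a 4-week change. A random walk continued to week 12 implies an SD of last-visit change of √174.1 = 13.2 points on a 66-point scale, which may be too much after a 4-week treatment. Milder structures give 5-6%.
- **The follow-up standard error is too small.** This follows only if a pooled within-subject error is used for visit contrasts, which the plan does not state. A contrast tested against its own error has no such bias.
- **The week-4 standard error is too wide.** This is not robust: the ratio was 1.04-1.40 in some recovery models but 0.91-0.96 under fast saturation.
- **Every FMA-UE result is affected.** The baseline-adjusted regression does not need sphericity.

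The four-level factor also conflicts with the three and two visits given elsewhere. That is a separate and firmer defect, and it changes the size of this one.

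**Conclusion.** The point holds in conditional form. The plan applies a univariate repeated-measures ANOVA at p < 0.05 to four visits whose differences are unlikely to have equal variance, and it names no correction or covariance model. If the uncorrected test is read and the spread of individual change grows appreciably with time, the group-by-time test has a size of about 6-10% with four visits and about 5.4-8% with three. Under compound symmetry, or with two visits, it is 5%. These figures rest on assumed covariances, since the article supplies none. Understatement of the follow-up standard error is a further possibility only if a pooled error is used. The outcomes exposed are MBI, ARAT, 9HPT and the follow-up comparison of FMA-UE; the FMA-UE regression is not.

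**What to change.** First reconcile the assessment times in Study design, Outcome measurements and Statistical analysis, since the number of visits determines the model. Then change the Statistical analysis section in one of two ways:

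1. **Preferred:** replace the ANOVA by a mixed model for repeated measures (SPSS MIXED) with group, visit and group-by-visit and an unstructured covariance. Take each visit's group difference and 95% CI from it. With four visits the covariance has 4×5/2 = 10 parameters.
2. **Minimum:** keep the ANOVA, state that Greenhouse-Geisser p-values are the ones used for time and group-by-time, and state that group comparisons at a visit use that visit's own error.

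Either needs one or two sentences and no new data or software. The price is slightly larger p-values and possibly a wider interval at follow-up.
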